### Recruitment and eligibility criteria

We will approach patients subjected exclusively to RYGB in regular clinical follow-up, aging 18 to 50 years and after at least 12 months from surgery. Our outpatients’ care unit follows at least 180 patients subjected to a bariatric procedure each year. Considering the inclusion and exclusion criteria, we expect to recruit 40 to 60 patients. The exclusion criteria will include regular physical exercise (≥ 3 days/week during 30 min) in the last 6 months; smoking; alcoholism; pregnancy; diagnosis or evidence of any cardiovascular; respiratory, neurological, infectious, endocrine, or musculoskeletal impairments that limit physical exercise; and or being in the use of any hormonal replacement therapy or medications that influence bone metabolism. Those who start some physical exercise program during the study, or with excess weight loss (EWL) < 50% (considered as primary non-responders) [28], or being in the use of drugs that interfere with weight, or who have performed a revisional bariatric surgery will also be excluded.

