### Randomization and experimental design

Sixty post-bariatric patients will be randomized through a random code generator software (www.randomization.com) at a ratio of 1:1 into two groups: (a) intervention group—that will perform a supervised RT program for 6 months—or (b) non-exercised control group—that will receive the standard clinical follow-up and shall not change their physical activity behavior. All patients will be followed by a multidisciplinary team (compose of endocrinologists, nutritionists, and physical educators) with expertise in post-bariatric patients, following the clinical practice guidelines [29]. Once the study is completed, for ethical reasons, the exercised control group will be invited to carry out the same RT program. Usual clinical care will be maintained for all patients following completion of the trial at our outpatients’ care unit.

The participants will visit our lab four times for data collection before and after 6 months post-intervention, with at least 24- to 48-h intervals between visits, as shown in Fig. 2. All assessments will be held in the morning between 7 and 11:00 am, in a quiet temperature-controlled environment (21–23 °C). The participants will be instructed to fast for 8 h for blood sample collections and vascular measures (at visit 2). The primary outcomes will be muscle mass and strength, bone metabolism biomarkers, BMD, and bone microarchitecture. The secondary outcomes will be anthropometry, hemodynamic measurement, metabolic/cardiovascular risk factors, health-related QoL, and endothelial function.

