### Sample size calculation and statistical analysis

In this study, it will be used a similar sample size previously used in a trial which provides 90% detection power between-group differences of BMD, with a significance level of 0.05 [54]. Descriptive analysis will consist of means and SD for continuous variables and percentages for categorical variables. Data normality will be tested by the Shapiro-Wilk test with the results expressed as mean ± SD or percentage, whenever appropriate. Baseline variables will be compared between the groups using either the Student *t*-test or chi-squared test. To compare dependent variables, a two-way ANOVA will be used considering group (intervention and non-exercised control groups) and time points (pre and post-intervention), followed by the Bonferroni post hoc test, in case of significant *F* ratios. An intention-to-treat analysis will be conducted, i.e., all participants, regardless of adherence to the intervention, will be included in the final analysis. No additional analyses are planned for the study. All calculations will be performed using the GraphPad™ software (version 6.0, La Jolla, CA, USA), and the significance level will be set at *P* ≤ 0.05.

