### Withdrawals of study and data/safety monitoring plan

The criteria for discontinuation will be (i) participant request, (ii) changes of clinical status during exercise sessions, (iii) absence ≥ 80% of training sessions, and (iv) engagement in another physical exercise program during the study. The principal investigator will oversee and monitor all elements of the trial, with contributions from co-investigators as needed. Patients who present any clinical adverse event during RT sessions will be conducted to the emergency room at our university hospital. Adverse clinical events will be reported to the ethics committee. The Data Monitoring Committee will consist of the principal investigator and co-investigators, who will perform meetings each month throughout the trial period to review data reports on recruitment, screening, baseline and post-interventions assessments, protocol adherence, adverse events, and safety. Since no anticipated problems which could be detrimental to the volunteers are expected in this trial, no interim analysis will be performed.

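### Excluding participants who start exercising during the study contradicts the promise to analyse everyone as randomised, and the withdrawal rules leave open whether follow-up continues

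*Protocol article*

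**What the plan says.** Three sections of the protocol article bear on who is analysed.

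- **Sample size calculation and statistical analysis.** The analysis is by intention-to-treat, explained as "all participants, regardless of adherence to the intervention, will be included in the final analysis". The same paragraph adds: "No additional analyses are planned for the study".
- **Recruitment and eligibility criteria.** A sentence opens with "Those who start some physical exercise program during the study", goes on to poor excess weight loss and use of drugs affecting weight, and closes with those "who have performed a revisional bariatric surgery will also be excluded". The closing verb governs every item in the list.
- **Withdrawals of study and data/safety monitoring plan.** Besides participant request, the discontinuation criteria are "changes of clinical status during exercise sessions", "absence ≥ 80% of training sessions" and "engagement in another physical exercise program during the study".

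Randomization and experimental design sets the control condition: controls "shall not change their physical activity behavior". It also plans the assessments after 6 months.

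**The concern.** An exclusion criterion is sound when it describes a person before randomisation. Starting an exercise programme during the study describes behaviour that can arise after it, and the allocated arm may influence that behaviour. In the control arm it is exactly the departure from assigned treatment that intention-to-treat is meant to keep in the comparison.

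What is at stake is the randomised comparison for every outcome. With 60 patients allocated 1:1 there are 30 per arm, so three removals are already 10% of an arm. If those removed differ in prognosis from those who stay, the remaining groups are no longer comparable by design. The withdrawals section adds uncertainty, because two of its criteria can be met only by people who have training sessions to attend.

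**Working it through.** **Step 1. When and where each rule can act.**

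| Rule | Section | Timing | Arm |
|---|---|---|---|
| Starts an exercise programme during the study | Eligibility (excluded) | can be after randomisation | either |
| Engages in another exercise programme | Withdrawals (discontinued) | after randomisation | either |
| Clinical change during sessions | Withdrawals (discontinued) | after randomisation | training only |
| Absence from training sessions | Withdrawals (discontinued) | after randomisation | training only |
| Participant request | Withdrawals (discontinued) | any time | either |
| Weight-loss response, weight-affecting drugs, revisional surgery | Eligibility (excluded) | can be applied at screening | not applicable before allocation |

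**Step 2. One case.** Take a control who joins a gym in month 2. The eligibility section excludes this person. The statistical section includes this person, because non-adherence is no ground for omission. The withdrawals section discontinues this person and is silent on the analysis. The first two instructions cannot both be followed.

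**Step 3. Readings that might remove the conflict.**

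- The clause could be meant only for the interval between enrolment and allocation. The text does not limit it so, and its reappearance among the discontinuation criteria points to the intervention period.
- It could define a secondary, adherers-only set. The statement that no further analyses are planned rules this out.

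**Step 4. Scale, under assumptions.** No removal rate or prognostic gap is given, so this is illustration only. Suppose a share p_C of controls is removed who would have done g SD better than the controls who stay, and a share p_T of trainees is removed who would have done g SD worse than the trainees who stay. With no true effect,

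shift towards training = p_C × g + p_T × g.

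- Middle case: 0.20 × 0.5 + 0.10 × 0.5 = 0.15 SD.
- Low end: 0.10 × 0.3 + 0 × 0.3 = 0.03 SD.
- High end: 0.30 × 0.5 + 0.10 × 0.5 = 0.20 SD.

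The sign is built into these assumptions. If instead 10% of trainees were removed for taking up another programme and would have done 0.5 SD better, that alone moves the difference 0.10 × 0.5 = 0.05 SD the other way.

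For comparison, the article claims 90% power at a 0.05 level but gives no effect size, SD or dropout, so its figure cannot be reproduced. With 30 per arm, a two-sided test and the normal approximation, the standardised difference detectable with 90% power is (1.960 + 1.282) × √(2/30) = 0.84. The high end is 0.20/0.84, about 24% of that, and the low end 0.03/0.84, about 4%.

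**Step 5. Reach of the absence rule.** Three sessions a week over 24 to 26 weeks (6 months) is 72 to 78 sessions. Eighty per cent is 57.6 to 62.4, so 58 to 63 missed sessions. Counted against all planned sessions, someone who never attends reaches this only after 58/3 ≈ 19 to 63/3 = 21 weeks. As written, the rule touches only near-total non-attenders.

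**The case against.** The strongest defence is that the statistical section alone defines the analysis set, and does so explicitly. On that view, exclusion in the eligibility section means only that the person stops taking part, and discontinuation means only that training stops. Both can coexist with intention-to-treat. The article is also condensed, so follow-up after discontinuation may be set out in the full protocol.

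Much of this stands. Discontinuation criteria do not in themselves remove anyone from an analysis, and a reader who infers that the withdrawals section breaches intention-to-treat goes further than the text. Its heading speaks of withdrawal from the study, but that creates an ambiguity, not a contradiction.

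The defence fails for the eligibility clause. That clause says excluded, without qualification, for an event that is non-adherence in one arm. If exclusion did mean leaving the study before the 6-month visits, the person would have no post-intervention measurement to include, and the promise would still not be met.

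Three stronger inferences are tempting and unsupported:

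- **That the bias favours training.** Starting outside exercise may be commoner among controls, who have no programme, but the documents do not say so, and the criterion applies to both arms.
- **That the planned ANOVA cannot retain people without a post value, so a mixed model or imputation is needed.** The article names a two-way ANOVA by group and time and does not call it repeated-measures. Handling of missing values is commonly left to the full protocol or analysis plan.
- **That the analysed groups will differ from the randomised ones.** They could, if the exclusion is carried out.

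**Conclusion.** The point holds as a contradiction between the eligibility section and the intention-to-treat statement. The withdrawals section is a related ambiguity to be cleared up with it. The conclusion rests on the wording alone and needs no figure. If the exclusion were applied, randomisation would no longer protect the comparison. How far and in which direction results would move cannot be derived from the documents. The 0.03 to 0.20 SD range depends wholly on the assumed removal rates, gaps and signs. Because the analysis set underlies every primary outcome, the conflict should be settled before the first participant is randomised.

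**What to change.** - Delete the during-study exercise clause from the exclusion criteria.
- State that the other exclusions in that sentence are applied at screening, before randomisation.
- Reconcile the eligibility and withdrawals sections with the statistical section by stating that, whatever the discontinuation criteria are, every randomised participant who has not withdrawn consent is invited to the 6-month assessments and analysed in the assigned arm.

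The clinical stopping criteria themselves are for the investigators, and no change to them is proposed.

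The cost is protocol wording. The 6-month visits are already planned, and the article describes the trial as not yet recruiting. The downside is that keeping controls who take up exercise, and trainees who do not attend, may dilute the estimated effect through contamination and non-adherence.

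### The protocol promises an analysis of all participants, but its only outcome analysis compares the groups on patients with a 6-month reading, so a completers' result could be reported as intention-to-treat

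*Protocol article*

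**What the plan says.** Under the heading Sample size calculation and statistical analysis, the protocol article fixes three things:

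- **Population.** The analysis is intention-to-treat: "all participants, regardless of adherence to the intervention, will be included in the final analysis".
- **Method.** For the dependent variables, "a two-way ANOVA will be used considering group (intervention and non-exercised control groups) and time points (pre and post-intervention"), with Bonferroni post hoc tests after a significant F ratio.
- **Closure.** "No additional analyses are planned for the study".

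Under the heading Randomization and experimental design, data are collected "before and after 6 months post-intervention". No intermediate outcome reading is stated. Sixty patients are randomised 1:1.

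Under the heading Withdrawals of study and data/safety monitoring plan, "The criteria for discontinuation will be (i) participant request, (ii) changes of clinical status during exercise sessions". The list continues with (iii) missed training sessions and (iv) "engagement in another physical exercise program during the study". Under the heading Recruitment and eligibility criteria, patients who start an exercise programme during the study are to be excluded. Neither section says whether a discontinued patient still attends the 6-month assessment.

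**The concern.** The promise, the method and the closing sentence do not fit together once any 6-month reading is absent. With one reading before and one after, a patient who misses the second has nothing to enter into the between-group contrast.

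Such absences are foreseeable. Of the four discontinuation criteria, a clinical change during an exercise session and absence from training sessions can occur only in the training arm. Loss may therefore be unequal between arms and related to how well training is tolerated. The contrast would then describe those who stayed, while the report would describe it as covering everyone randomised. The same ANOVA serves the primary muscle and bone outcomes, so all of them would be affected.

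**Working it through.** **Inputs from the protocol article:** 60 patients, 30 per arm; one pre and one post reading; group-by-time two-way ANOVA; significance level 0.05; 90% power claimed for BMD by reference to an earlier trial. The article gives no effect size, SD, pre-post correlation or dropout rate, so its sample size cannot be reproduced. Everything below that depends on loss is an assumption.

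**Step 1: what the ANOVA uses.** With two groups and two time points, the repeated-measures group-by-time F equals the squared two-sample t on change (post minus pre). On a test data set the two agreed: F = 4.0449 and t² = 4.0449. A patient without a post reading has no change score and drops out of the test.

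**Step 2: the other reading.** The article does not use the words repeated-measures. An ordinary two-way ANOVA would accept a baseline-only patient, but only by treating paired readings as independent, which is the wrong error term. The 6-month comparison would still rest only on patients measured at 6 months.

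**Step 3: loss at random.** There is no bias in expectation. In 4,000 simulated trials per setting (30 per arm, pre-post correlation 0.8, no true effect, loss of 10 to 30% from the training arm), the mean estimate stayed at zero and the type I error was 4.4 to 5.5%. The cost is power:
- Difference detectable with 90% power at 30 per arm: √(2/30) × (1.960 + 1.282) = 0.84 SD.
- With loss in both arms, power ≈ Φ(3.242 × √(1 − f) − 1.960).
- At f = 10%, 20% and 30% this gives about 87%, 83% and 77%.

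**Step 4: loss that depends on baseline.** Suppose the lowest fraction f at baseline leaves the training arm.
- Rise in mean baseline among those who stay: φ(z_f)/(1 − f). At f = 20%, 0.280/0.80 = 0.35 SD.
- Bias of the change contrast: (ρ − 1) × 0.35.
- ρ = 0.7: −0.105, or about −0.10 SD. ρ = 0.9: −0.035 SD.

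The sign is against training if higher values are better. A simulation at 30 per arm gave the same values. A model that constrains the baseline means to be equal removed the bias.

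**Step 5: loss that depends on response.** The setting is as in step 3, with an assumed correlation of 0.5 between a patient's change and staying in the training arm.

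| Loss in training arm | False benefit | Type I error |
|---|---|---|
| 10% | 0.06 SD | about 7% |
| 20% | 0.11 SD | about 10% |
| 30% | 0.16 SD | about 14% |

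The sign is now in favour of training. A check of the baseline-constrained model in this setting left most of the bias in place, because baseline says little about who leaves. This is why a sensitivity analysis is also needed.

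**The case against.** **Missing-data handling is commonly left to the full protocol or SAP.** This stands as far as it goes: silence on a missing-data method would not be a finding. But this article states the population, names one method and closes the list. An analyst who follows the text as written obtains a completers' contrast under an intention-to-treat label.

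**The closing sentence may mean only that no subgroup or adjusted comparisons are planned, and imputation before the ANOVA would keep all 60 patients with the pairing intact.** Both are fair. A reader might infer that the ANOVA can never include a patient without a second reading. The documents do not support that, since imputation is neither mentioned nor expressly forbidden. What stands is that no such step is stated, and the closing sentence at least discourages one.

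**Discontinued patients may still be measured.** The intention-to-treat sentence is about adherence, and the discontinuation list does not say that assessments stop. If everyone is measured at 6 months, the promise can be kept with the stated ANOVA. A reader might infer that a mislabelled completers' analysis is certain, but the documents show only that it is possible and unguarded against.

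**A reader might also infer that the training effect will be overstated by a known amount.** If a fraction f of the training arm is unmeasured and would have had control-like outcomes, the ratio is 1/(1 − f) − 1, or 11%, 25% and 43% at f = 10%, 20% and 30%. These figures only restate the assumption, and the documents give neither f nor those outcomes. Step 4 of the working gives the opposite direction.

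**Conclusion.** The point holds in a limited form. As written, the named analysis compares the groups on patients with a 6-month reading, while the text promises all participants. The article foresees withdrawals, some possible only in the training arm, and does not provide for measuring those patients. The result could therefore be a completers' comparison reported as intention-to-treat.

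Neither the size nor the direction of any bias is established. It ranges from none under random loss, through about −0.10 or −0.035 SD under 20% baseline-dependent loss (correlation 0.7 or 0.9), to a false benefit if poorer responders leave. All of these rest on assumed loss patterns. If no 6-month reading is missing, there is no harm. The correction is worth making because it is cheap and the mismatch touches every primary outcome.

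**What to change.** 1. Replace the ANOVA sentence with a linear mixed model for each outcome on all randomised participants, using all available readings, with a common baseline mean and the group contrast at 6 months.
2. State that participants who stop training are still invited to the already planned 6-month assessment. Reconcile this with the discontinuation list and with the eligibility section's exclusion of those who start exercising during the study.
3. Report the number of missing 6-month readings per arm, with reasons.
4. Add control-based imputation of missing training-arm values as a sensitivity analysis, and amend the sentence that no additional analyses are planned so that it allows this. It should not be the primary analysis, because it assumes that unmeasured trained patients gained nothing over controls, which is a strong and deliberately conservative choice.
5. If the ANOVA is kept, call it a complete-case analysis and drop the claim that all participants are included.

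The cost is revised wording and a little more analysis work, and possibly a less favourable estimate. No extra patients or procedures are needed, and the article's trial status section says that recruitment had not begun.

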### Withdrawals of study and data/safety monitoring plan

The criteria for discontinuation will be (i) participant request, (ii) changes of clinical status during exercise sessions, (iii) absence ≥ 80% of training sessions, and (iv) engagement in another physical exercise program during the study. The principal investigator will oversee and monitor all elements of the trial, with contributions from co-investigators as needed. Patients who present any clinical adverse event during RT sessions will be conducted to the emergency room at our university hospital. Adverse clinical events will be reported to the ethics committee. The Data Monitoring Committee will consist of the principal investigator and co-investigators, who will perform meetings each month throughout the trial period to review data reports on recruitment, screening, baseline and post-interventions assessments, protocol adherence, adverse events, and safety. Since no anticipated problems which could be detrimental to the volunteers are expected in this trial, no interim analysis will be performed.

### Data collection, management, and dissemination

Checklists will be developed to guarantee the quality and completeness of the data and procedures. In order to keep confidentiality, all participants’ data will be coded with study ID and stored in folders, checked for completeness by the principal investigator, and will not be passed on to any third party without consent from participants. Study copy documentation will be stored securely at the university with restricted access, during and after the completion of the study and after data publication. Each participant will receive a full report containing his/her assessment results and information about physical exercise recommendations at the end of the study [55]. The results of the trial will be publicized in scientific congresses and journals.

